**Abstract of the Protocol**

|Study Design|□ Case-Control Study □ Cohort Study □ Cross-Sectional Study|
**☑**Randomized Controlled Trial (Blinding Applied) □ Other:|
|Study Type| (Category A: High Risk)|
|(Please select according to the project type)|□ Class III Clinical New Technology (Definite safety and efficacy, high technical difficulty and risk)|
|□ Special Population Study (Children, pregnant women, individuals with intellectual disabilities,

patients with mental disorders, etc.)|
|□ Off-Label Drug Study (□ Off-indication □ Off-route of administration □ Off-dose □ Off-age|
|□ Off-contraindication □ Off-population □ Other, please specify: )|
|□ Off-Label Device Study (□ Off-indication □ Off-use range □ Off-contraindication □ Off-population)|
|□ Other (Please specify: )|
|□ (Category B: Medium Risk)|
|□ Post-marketing Biologics Study (Preventive and therapeutic)|
|□ Post-marketing Therapeutic Vaccine Study|
|□ Post-marketing Orphan Drug Study|
|□ Class II Clinical New Technology (Definite safety and efficacy, certain technical difficulty, certain medical and ethical risks)|
|□ Other (Please specify: )|
|□ (Category C: Low Risk)|
|□ Post-marketing Drug Study (Including chemical drugs, generic drugs, etc.)|
|□ Post-marketing Device Study (Including AI, imaging software)|
|**☑**(Class I Clinical New Technology (Definite safety and efficacy, low technical difficulty, virtually no ethical risk in medical technology)|
|□ Other (Please specify: )|
|Total Number of Cases|486|
|Risk/Benefit Analysis|Adjusting blood flow rate affects filter lifespan without posing risks to patients|
|Risk Assessment|□ No greater than minimal risk (**☑**Greater than minimal risk)|
|Minimal risk: Refers to the possibility and extent of risks in the trial not exceeding those of daily life, or undergoing routine physical examination or psychological testing|

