**III. Research Design, Methods, and Steps**

1. **Research Design**
   - **Study Type:** Single-center, single-blind, prospective randomized controlled trial (RCT)
   - **Randomization Method:** Each patient meeting the inclusion criteria will be randomly assigned to one of three groups (low blood flow rate group, medium blood flow rate group, or high blood flow rate group) by a study coordinator using a computer-generated random number table. Randomization will be conducted in a 1:1:1 ratio to ensure equal numbers of patients in each group, thereby maximizing the balance of patient characteristics and potential confounding factors across the groups. The study coordinator will not be involved in patient treatment or data collection and analysis. Group assignment information will be strictly confidential to ensure fairness. Each patient's randomization information will be recorded in a dedicated study database with appropriate security measures to prevent unauthorized access. All relevant researchers will receive training on the proper handling of randomization information. During patient selection and treatment, only authorized researchers will have access to group assignment information. These authorized personnel, including the principal investigator and the physician assigning treatment, will access the information through an encrypted electronic system to ensure data security and privacy. Unauthorized researchers will not have access to group assignment information to maintain the integrity of the single-blind design. All treatment and patient management decisions will be made by authorized personnel based on group assignment information and clinical conditions.
   - **Research Center:** West China Hospital, Sichuan University

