   - **Sample Size Calculation:** The primary outcome measure of this study is filter lifespan. Therefore, filter consumption quantity is selected for sample size calculation. Based on retrospective and prospective cohort study data from our center, the smallest difference in filter lifespan was observed between the 200 mL/min and 250 mL/min blood flow rate groups. Thus, the maximum possible sample size can be calculated based on the lifespan difference between these two groups. Previous study results showed that the average filter lifespan was 28.09 ± 21.15 hours in the 200 mL/min blood flow rate group and 35.51 ± 17.97 hours in the 250 mL/min blood flow rate group. With a significance level (α) set at 0.05 and power at 0.90, the software PASS (Power Analysis and Sample Size Software) version 15 was used to calculate a sample size of N = 153 per group. Considering a dropout and refusal rate of 5%, the final number of filters required per group is at least 162, totaling at least 486 filters.
2. **Research Methods**

Patients undergoing CRRT at West China Hospital who meet the inclusion and exclusion criteria will be randomly divided into three groups: low blood flow rate group, medium blood flow rate group, and high blood flow rate group. The international standard blood flow rate for anticoagulant-free CRRT is 250 mL/min, while the standard blood flow rate for anticoagulant-free CRRT at our center is 200 mL/min. For hemodynamically unstable patients or those with high circuit pressure, our center reduces the blood flow rate to 150 mL/min based on experience, which is consistent with previous studies defining 150 mL/min as the low blood flow rate group [1]. Therefore, we define 150 mL/min, 200 mL/min, and 250 mL/min as the low, medium, and high blood flow rate groups, respectively.

- **Low Blood Flow Rate Group:** Adjust the CRRT blood flow rate to 150 mL/min.
- **Medium Blood Flow Rate Group:** Adjust the CRRT blood flow rate to 200 mL/min.
- **High Blood Flow Rate Group:** Adjust the CRRT blood flow rate to 250 mL/min.

The remaining CRRT prescription and parameter adjustments will be determined based on the patient's actual condition, experienced clinical physicians, and CRRT specialists. If during CRRT, high blood flow rate causes high vascular access pressure and requires a reduction in blood flow rate, the following principles will be followed:

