**IV. Case Selection**

1. **Inclusion Criteria**
   1. Patients undergoing CRRT;
   2. Age 18 years or older;
   3. No anticoagulant used during CRRT;
   4. Informed consent provided by the patient or their legal guardian/agent.
2. **Exclusion Criteria**
   1. Patients with severe coagulation disorders or undergoing anticoagulant therapy;
   2. Patients receiving intermittent renal replacement therapy (IRRT) or other non-CRRT treatments;
   3. Pregnant women.
3. **Criteria for Study Termination**
   1. **Safety Issues:** Serious adverse events: If during the study, the incidence of serious adverse events related to treatment such as hypotension, malignant arrhythmias, or death is significantly higher in one group compared to the other two groups, or exceeds the predefined safety threshold, consideration should be given to terminating that group's study. The safety threshold is set based on data from similar previous studies and the opinions of clinical experts to ensure patient safety. For example, if the incidence of bleeding events exceeds 10% and is 5% or more higher than the other groups; the incidence of thrombotic events exceeds 5% and is 3% or more higher than the other two groups; the incidence of infectious events exceeds 15% and is 5% or more higher than the other groups; the incidence of cardiovascular events exceeds 8% and is 4% or more higher than the other two groups [2,3].
   2. **Inadequate Effectiveness:** Interim analysis: Interim analysis will be conducted after 50% of the patients have been enrolled, performed by an independent statistician who is blinded to treatment allocation.
   3. **Interim Analysis Objectives:** To assess filter lifespan in different blood flow rate groups, compare filter blockage rates among groups, and evaluate the incidence of adverse events.
   4. **Interim Analysis Indicators:** Primary outcome measure: Filter lifespan (hours); Secondary outcome measures: Filter clotting rate, incidence of adverse events (bleeding, thrombus formation, etc.).
   5. **Interim Analysis Method:** Kaplan-Meier survival analysis will be used to assess filter lifespan, and the Log-rank test will be used to compare differences in filter lifespan among different groups. The chi-square test will be used to compare differences in filter blockage rates and adverse event incidence among groups.

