**VI. Detection Items and Time Points**

1. **Baseline Data:** At the time of patient admission, detailed records will be kept of demographic characteristics, laboratory indicators, examination results, primary disease, comorbidities, concomitant medications, blood pressure, etc.
2. **Filter Lifespan:** Each time a filter is replaced, the usage time of each filter will be recorded. Filters will be replaced based on the following criteria: obvious clotting in the filter, catheter, or venous chamber; filter usage time exceeding 72 hours (even if there are no other issues); patient needs to stop the machine for an outside examination or other treatments; treatment goals are achieved or CRRT is terminated.
3. **CRRT-Related Parameters:** After the CRRT prescription is established, detailed records will be kept of the CRRT prescription, including ultrafiltration rate, access, mode, etc. If the blood flow rate is reduced due to poor circuit performance or the anticoagulation method is adjusted due to coagulation function, the time, adjustment amount, and changes before and after adjustment will be recorded in detail.
4. **Filter Performance and Efficacy:** After CRRT is completed, the filter clearance performance will be recorded, including creatinine clearance, urea nitrogen clearance, cystatin C, and ultrafiltration rate.
5. **Patient Physiological Parameter Changes:** During CRRT, arterial blood pressure will be monitored every 2 hours, and the occurrence of hypotension and other hemodynamic instability events will be recorded.
6. **Adverse Events:** During CRRT, any adverse events that occur will be observed and recorded, including thrombus formation, bleeding complications, etc.
7. **Clinical Outcomes:** After CRRT is stopped, the patient's renal function recovery will be monitored, such as changes in creatinine and glomerular filtration rate. After discharge, the patient's survival status and hospital stay duration will be recorded.

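### Patients are randomised but the trial is sized as 486 independent filters, a number the abstract calls cases; if it means filters, the stated 90% power is unsupported.

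*Protocol*

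**What the plan says.** The unit changes from place to place in the protocol.

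- **Randomisation (section III, Randomization Method):** "Each patient meeting the inclusion criteria will be randomly assigned to one of three groups". The allocation sentence also counts patients: "Randomization will be conducted in a 1:1:1 ratio to ensure equal numbers of patients in each group".
- **Sample size (section III, Sample Size Calculation):** the basis is described as "filter consumption quantity is selected for sample size calculation", although the inputs are lifetimes: "the average filter lifespan was 28.09 ± 21.15 hours in the 200 mL/min blood flow rate group", against 35.51 ± 17.97 hours at 250 mL/min. With alpha 0.05 and power 0.90 this gives 153 per group. After a 5% allowance for dropout and refusal, "the final number of filters required per group is at least 162, totaling at least 486 filters".
- **Abstract:** "Total Number of Cases|486".
- **Interim (section IV, Criteria for Study Termination):** "Interim analysis will be conducted after 50% of the patients have been enrolled".
- **Data (section VI, Filter Lifespan):** "Each time a filter is replaced, the usage time of each filter will be recorded". Nothing restricts the endpoint to a patient's first filter.
- **Analysis (sections IV and XI):** Kaplan-Meier and Cox for lifespan, log-rank for lifespan at the interim, and chi-square for filter blockage at the interim. No term for repeated filters within a patient is named.

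**The concern.** Filters used in one patient share that patient's coagulation state, vascular access and illness, so their lifetimes are likely to be positively correlated. A set of 162 filters from fewer than 162 patients then carries less information than 162 independent observations, and the sample size section makes no allowance for this.

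Three things are at stake. The first is the stated power for the smallest expected contrast, 200 against 250 mL/min. The second is the type I error of filter-level tests; the interim tests also feed rules that can close an arm or stop the trial at P < 0.05. The third is practical: the protocol does not settle when recruitment ends or when the interim falls, because no patient target exists unless 486 is one.

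**Working it through.** **Inputs from the protocol.** Means 28.09 and 35.51 h; SDs 21.15 and 17.97 h; alpha 0.05 (taken as two-sided, since the protocol does not say); power 0.90; 5% loss; 153, 162 and 486.

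**Inputs assumed.** Filters per patient (m) and within-patient ICC. Neither is in the protocol, so a range is shown.

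**Step 1: reproduce the plan's figure.**
- Difference = 35.51 − 28.09 = 7.42 h.
- Pooled SD = √((21.15² + 17.97²)/2) = 19.62 h.
- Normal formula: n = 2 × 19.62² × (1.960 + 1.282)² / 7.42² = 147 per group. The t-based answer is 148.
- Rank-test variant (multiply by π/3): 154 to 155.
- The stated 153 lies between these. Its t-based power is 0.909, so it is adequate for independent units.
- 153/0.95 = 161.05, rounded up to 162; 3 × 162 = 486.

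None of these formulas contains a clustering term.

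**Step 2: power if 486 counts filters.** Design effect DE = 1 + (m − 1) × ICC, and effective n = 153/DE. Power (noncentral t) is for a test that allows for clustering. The last column is for the alternative, a test that ignores it: error = 2 × (1 − Φ(1.96/√DE)).

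| m | ICC | DE | Effective n per group | Power, clustered test | Type I error, unadjusted test |
|---|---|---|---|---|---|
| 1 | any | 1.00 | 153 | 0.91 | 5.0% |
| 1.5 | 0.05 | 1.025 | 149.3 | 0.90 | 5.3% |
| 2 | 0.1 | 1.10 | 139.1 | 0.88 | 6.2% |
| 2 | 0.3 | 1.30 | 117.7 | 0.82 | 8.6% |
| 3 | 0.3 | 1.60 | 95.6 | 0.74 | 12.1% |

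Power drops below 0.90 once DE passes about 1.03 (153/148) on the t formula, or 1.04 (153/147) on the normal formula. The DE formula assumes equal numbers of filters per patient.

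**Step 3: check the error with the test the protocol names.** An unadjusted three-arm log-rank test was simulated under no effect (lognormal lifetimes, 72 h cap, random censoring, about 153 filters per arm, 3000 runs, ICC on the log scale). It rejected in 5.3% of runs at m = 1, 5.7% at m = 2 with ICC 0.1, 7.7% at m = 2 with ICC 0.3, and 12.8% at m = 3 with ICC 0.3. This agrees with the formula in direction and rough size.

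**Step 4: filter numbers by arm.** At the plan's means, the 200 mL/min arm uses 35.51/28.09 = 1.26 times as many filters per CRRT hour as the 250 mL/min arm. With an assumed 72 h of CRRT per patient, 80 patients per arm give 80 × 72/35.51 = 162 filters at 250 mL/min and 80 × 72/28.09 = 205 at 200 mL/min. Equal patient numbers therefore do not give equal filter numbers, but both arms reach the minimum of 162.

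**Step 5: interim timing.** If 486 is patients, half is 243 patients. If it is filters, the patient total is 486/m: 243 at m = 2 and 162 at m = 3, so half is about 122 or 81 patients.

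**The case against.** The best defence is that 486 really means patients. The abstract counts cases, the interim counts patients, and the loss allowance covers refusal, which applies to patients and not to filters. On that reading the trial has at least 162 patients per group and power is not short. This stands, and it makes the power shortfall conditional. It does not remove the contradiction, because the sample size section says filters explicitly.

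Second, independence is explicit only in the sample size formula. Cox regression with patient-clustered variance is still Cox regression, and an SAP, not shown here, could specify it. This also stands: a reader might infer that the final analysis will treat filters as independent, but the protocol does not say so. An SAP could repair the error rate. It would not by itself supply the power stated for 486 filters.

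Third, the size of the loss rests on assumed values, and light clustering (1.5 filters, ICC 0.05) costs almost nothing. That is correct, and the range above includes it.

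Two stronger readings are tempting but unsupported. One is that 1:1:1 allocation of patients cannot yield 162 filters in each group. The protocol's figure is a minimum, and step 4 shows it can be met. The other is that the planned ANOVA has the same fault. Section XI uses ANOVA for filter performance indicators, not lifespan, and section VI records those after CRRT is completed, which does not establish repeated values per patient.

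**Conclusion.** The point holds in conditional form. The mismatch between the randomised unit and the counted unit, and the two meanings of 486, are in the text and need no assumption.

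If 486 means filters and patients contribute several correlated filters, the stated 90% power is unsupported: between about 0.90 and 0.74 over the assumed range of 1.5 to 3 filters per patient and ICC 0.05 to 0.3. If 486 means patients, power is not short.

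Under either reading, log-rank, Cox or filter-blockage chi-square tests on all filters would exceed 5% if they ignore the patient, at about 5% to 12% over the same range. The power loss and the inflated error belong to alternative analyses and do not add up. A reader might infer that both the 90% power and the 5% error have definitely failed. The documents do not support that, because the unit is ambiguous, the clustering is not quantified and the variance method is not stated.

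**What to change.** 1. State one unit for 486, use it in both the abstract and the sample size section, and time the interim in that unit.
2. Use patient-clustered (robust) variance or a patient-level bootstrap for every filter-level comparison, including the interim log-rank and blockage tests.
3. If the unit is filters, keep the size and restate the power, taking filters per patient and ICC from the centre's own cohort that supplied the means and SDs.
4. If the unit is patients, say so. Two primary analyses are then valid: the first filter per patient (independent, 162 per group), or all filters with clustered variance. First-filter-only is an option, not a requirement.
5. Note that filter numbers will differ between arms under equal patient allocation.

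The cost is a change of wording, a variance option in standard software and one look at existing cohort data. The downside is a less favourable stated power if the unit is filters. Restating it makes the figure honest but does not restore 90%. If first filters become primary, later filters move to a secondary analysis.

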**IV. Case Selection**

1. **Inclusion Criteria**
   1. Patients undergoing CRRT;
   2. Age 18 years or older;
   3. No anticoagulant used during CRRT;
   4. Informed consent provided by the patient or their legal guardian/agent.
2. **Exclusion Criteria**
   1. Patients with severe coagulation disorders or undergoing anticoagulant therapy;
   2. Patients receiving intermittent renal replacement therapy (IRRT) or other non-CRRT treatments;
   3. Pregnant women.
3. **Criteria for Study Termination**
   1. **Safety Issues:** Serious adverse events: If during the study, the incidence of serious adverse events related to treatment such as hypotension, malignant arrhythmias, or death is significantly higher in one group compared to the other two groups, or exceeds the predefined safety threshold, consideration should be given to terminating that group's study. The safety threshold is set based on data from similar previous studies and the opinions of clinical experts to ensure patient safety. For example, if the incidence of bleeding events exceeds 10% and is 5% or more higher than the other groups; the incidence of thrombotic events exceeds 5% and is 3% or more higher than the other two groups; the incidence of infectious events exceeds 15% and is 5% or more higher than the other groups; the incidence of cardiovascular events exceeds 8% and is 4% or more higher than the other two groups [2,3].
   2. **Inadequate Effectiveness:** Interim analysis: Interim analysis will be conducted after 50% of the patients have been enrolled, performed by an independent statistician who is blinded to treatment allocation.
   3. **Interim Analysis Objectives:** To assess filter lifespan in different blood flow rate groups, compare filter blockage rates among groups, and evaluate the incidence of adverse events.
   4. **Interim Analysis Indicators:** Primary outcome measure: Filter lifespan (hours); Secondary outcome measures: Filter clotting rate, incidence of adverse events (bleeding, thrombus formation, etc.).
   5. **Interim Analysis Method:** Kaplan-Meier survival analysis will be used to assess filter lifespan, and the Log-rank test will be used to compare differences in filter lifespan among different groups. The chi-square test will be used to compare differences in filter blockage rates and adverse event incidence among groups.
   6. If the interim analysis results show that the filter lifespan in any group is significantly lower than the other groups (P < 0.05), and the incidence of adverse events is significantly increased, enrollment of patients in that group will be terminated. If there is no significant difference in filter lifespan among all groups (P > 0.05), and no significant difference in adverse event incidence, the study will continue until all patients have been enrolled.
   7. The statistician will report to the independent Data and Safety Monitoring Board (DSMB), which will review and assess the interim analysis data and provide recommendations to the researchers on whether to continue, modify, or terminate the study [4][5].
   8. **Achievement of Statistical Significance:** If the interim analysis shows a significant difference in filter lifespan among different blood flow rate groups (P < 0.05), and this difference is sufficient to prove the primary research hypothesis, the study may be terminated early.
   9. **Participant Request to Withdraw:** If a participant requests to withdraw from the study.

**Termination Procedure:** Upon receiving the DSMB's recommendation, the study leader should immediately suspend enrollment of new patients and notify all research centers; inform the Institutional Review Board (IRB) and relevant regulatory authorities, providing the reasons for termination and the interim analysis results; provide appropriate follow-up treatment and follow-up for patients already enrolled.

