**VII. Efficacy Evaluation Criteria**

1. **Efficacy Evaluation:** Measure the impact of blood flow rate on filter lifespan in anticoagulant-free CRRT, recording each patient's blood flow rate, filter usage time, and any potential filter failures or blockages.
2. **Safety Evaluation:** Monitor adverse events related to blood flow rate adjustments, such as thrombus formation, bleeding, or filter failure, continuously monitoring and recording the occurrence and severity of adverse events in each patient. Use statistical methods to analyze the incidence of adverse events and compare them with different blood flow levels to assess their correlation.

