**VIII. Observation, Recording, and Management of Adverse Events**

In this study, adverse events refer to events during CRRT that cause CRRT to be urgently stopped or pose a life-threatening risk to the patient, with significant improvement after CRRT is stopped. Therefore, the observation of CRRT adverse events ends when the patient completely finishes multiple courses of CRRT.

Anticipated adverse events include hypotension, electrolyte imbalance, bleeding, or infection. The relationship between adverse events and study interventions is typically judged based on: 1) Temporal association: The event occurs within a specific time after CRRT initiation, or other causes of adverse events are excluded; 2) Known side effects of drugs or devices; 3) Whether the event disappears or alleviates after CRRT is stopped.

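### The arm-closure safety trigger counts serious events related to treatment, but the relatedness criteria and the adverse-event definition refer to CRRT, not to blood flow, and other rules in the protocol carry no such filter

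*Protocol*

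**What the plan says.** **The trigger.** Protocol Section IV, Criteria for Study Termination, item 1 applies when "the incidence of serious adverse events related to treatment such as hypotension, malignant arrhythmias, or death is significantly higher in one group" than in the other two, "or exceeds the predefined safety threshold, consideration should be given to terminating that group's study". Both limbs share one grammatical subject, the treatment-related serious events. The examples of the threshold that follow are worded differently: for instance, "the incidence of cardiovascular events exceeds 8% and is 4% or more higher than the other two groups", with no mention of relatedness or seriousness.

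**The relatedness criteria.** Section VIII lists what the judgement is typically based on: "The event occurs within a specific time after CRRT initiation, or other causes of adverse events are excluded"; known side effects of drugs or devices; and "Whether the event disappears or alleviates after CRRT is stopped". The same section defines an adverse event as one that forces an urgent stop of CRRT or threatens life, and that improves markedly once CRRT is stopped.

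**Other safety rules.** Item 6 of the termination criteria closes an arm if filter life is significantly shorter "and the incidence of adverse events is significantly increased, enrollment of patients in that group will be terminated". Section XI item 4 compares adverse-event incidence between arms by chi-square or Fisher tests. Neither mentions relatedness. Section VII item 2 opens with "Monitor adverse events related to blood flow rate adjustments" and then compares incidence across flow levels.

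**Who knows the arm.** Section III gives the allocation to the principal investigator and the physician assigning treatment, and says: "All treatment and patient management decisions will be made by authorized personnel based on group assignment information and clinical conditions". Section X has the principal investigator review adverse events cumulatively. Section VIII requires an assessment of association for each event but does not say who makes it.

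**The concern.** Only the flow rate is randomised. An event that follows the start of CRRT, or eases when CRRT ends, does so in every arm, so these criteria cannot tell an effect of 250 mL/min from an effect of CRRT. In a randomised comparison the difference between arms already carries the causal information. Filtering events by individual attribution first can only discard some of them or misclassify them.

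At stake is the trial's main safety brake. If part of a real excess at one flow rate is called unrelated, or falls outside the definition of an adverse event, the arm can stay open when the full count would have led to a review. And because the trigger can be read with or without the filter, two people applying it to the same data could reach different answers.

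**Working it through.** **1. Passages side by side.**

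| Place | What is counted | Relatedness filter? |
|---|---|---|
| IV, item 1, trigger sentence | Serious events, with death as an example | Yes |
| IV, item 1, threshold examples | Bleeding, thrombotic, infectious, cardiovascular events | Not stated |
| IV, item 6 (interim) | Adverse events, only jointly with shorter filter life | No |
| VII, item 2 | Opens with events related to flow adjustments, then incidence by flow level | Opening phrase only |
| XI, item 4 | Adverse events by arm | No |
| VIII, definition | Must improve after CRRT is stopped | Restricts every row that relies on the term |

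Two kinds of event show the gap. A death is named in the trigger, yet it cannot improve after CRRT stops. Section III also allows the flow to be lowered in 50 mL/min steps while CRRT continues. Harm that resolves that way is the event most clearly tied to flow, yet it meets neither the third relatedness criterion nor the improvement clause, because CRRT was not stopped.

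**2. Arm size.** The protocol's 153 per group with 5% loss gives 153/0.95 = 161.05, so 162, and 3 × 162 = 486, as stated. (The 153 itself: 2 × (1.960 + 1.282)² × 19.62²/7.42² gives 147; dividing by the rank-test efficiency 0.955 gives 154, close to 153.) The point does not depend on this. It only supplies n = 162, treated below as independent patients.

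**3. The limb that expressly carries the filter (significantly higher).** Assumed true rates are 10% and 20%, two-sided 0.05, with a share f called related in both arms. Power = Φ{[d√n − 1.96√(2p̄(1−p̄))]/√(p₁(1−p₁)+p₂(1−p₂))}, where p₁ = 0.10f, p₂ = 0.20f, d = p₂ − p₁ and p̄ is their mean.
- f = 1: (0.10 × 12.728 − 1.96 × 0.505)/0.500 = 0.57, power 71%.
- f = 0.75: power 57%.
- f = 0.50: (0.05 × 12.728 − 1.96 × 0.3725)/0.3708 = −0.25, power 40%.
- f = 0.25: power 22%.
- With 81 per arm (half enrolled): 43%, 33%, 23% and 13%.

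**4. The threshold limb, reading the filter into the cardiovascular example.** With n = 162, more than 8% means at least 13 events (0.08 × 162 = 12.96), and 4 points means at least 7 more events than each other arm (0.04 × 162 = 6.48). The chance that the high-flow arm is flagged is Σ over x ≥ 13 of Pr(X₃ = x) × Pr(X₁ ≤ x − 7) × Pr(X₂ ≤ x − 7), with independent binomial counts. Assumed true rates are 7/7/14%.

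| Share called related, all arms | Observed rates | Flagged, n = 162 | Flagged, n = 81 |
|---|---|---|---|
| 100% | 7/7/14% | 72% | 59% |
| 70% | 4.9/4.9/9.8% | 48% | 41% |
| 50% | 3.5/3.5/7% | 24% | 23% |

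**5. What counting everything costs.** With equal true rates of 10% and n = 162, the same formula flags a given arm by chance in 4.3% of trials counting all events, 2.7% if 70% are counted and 1.3% if 50% are.

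**The case against.** Much of the case on the other side stands. Only the trigger sentence carries the filter expressly. The threshold examples, the interim rule and the Section XI comparison do not, and Section VI records any adverse event. A reader might infer that the whole safety evaluation passes through the relatedness judgement; the documents do not support that. The opening words of Section VII item 2 refer to flow adjustments and invoke no Section VIII judgement. The calculation in step 4 therefore rests on one reading of an ambiguous item.

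A reader might also infer that staff who know the arm judge relatedness and so could create a false signal against 250 mL/min. The protocol names no assessor. The sentence quoted from Section III concerns management decisions, and other researchers have no access to the allocation. Open attribution is plausible, since the principal investigator knows the arm and reviews events, but it is not stated. With equal attribution in all arms the filter creates no false excess. One arises only if attribution differs by arm: with equal true rates of 10%, calling 90% related at 250 mL/min and 50% elsewhere would raise flagging of that arm from 4% to 35%. Nothing in the protocol supports those shares.

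Further, item 1 only asks that closure be considered, and an independent monitoring board makes the recommendation. The relatedness list is described as typical, not exhaustive, and timing criteria might admit most events during CRRT, which would make the loss smaller than in the lower rows. If the improvement clause attaches only to life-threatening events, a death preceded by an emergency stop could still count; harm relieved by lowering the flow would still be missed.

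None of this removes the inconsistency. The unfiltered interim route is no substitute, because it also requires shorter filter life, and a board cannot weigh events that never reach its count.

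**Conclusion.** The concern holds in a limited form. The trigger in item 1 depends on a relatedness judgement that cannot isolate the randomised factor. The adverse-event definition excludes, or may exclude, two kinds of event that matter most for it. The same item and later sections count events without that filter, so the rule is not determinate.

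The loss of signal needs no unblinding and no bias. Under assumed rates, the chance of flagging a true doubling falls from 72% to 48% or 24%, and power for a significant difference from 71% to 57% or 40%, depending on the share called related. The event rates and attribution shares are assumptions, since the protocol gives none; the direction of the loss under equal attribution does not depend on them. That harm is manufactured by staff who know the arm remains a possibility the protocol leaves open, not a finding. This should be corrected, but it does not undermine the between-arm analysis in Section XI, apart from the narrow definition of an adverse event.

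**What to change.** Reconcile Section IV items 1 and 6, Section VII item 2, Section VIII and Section XI item 4 as follows.

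- State that the arm-termination comparison counts all serious events by randomised arm, regardless of attribution, and remove the relatedness wording from item 1 and from the opening of Section VII item 2.
- Remove the condition of improvement after CRRT is stopped from the definition of events counted for that comparison. Without this step, deleting the relatedness wording leaves the restriction in place.
- Keep the causality judgement for individual case reporting, refer it to the assigned flow rate as well as to CRRT, and name who makes it and whether that person knows the arm.

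The numerical thresholds are for the sponsor and the monitoring board to settle; none is proposed here.

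The cost is mainly wording. Section VIII already requires every adverse event to be documented, and Section VI already collects blood pressure, hypotension and survival, so little new data should be needed once the definition is widened. The downside is that background events of critical illness enter every arm. Absolute incidences will be higher, and chance flagging rises slightly (for example from 1.3% or 2.7% to 4.3% for a given arm in step 5), which the board should bear in mind when it reviews the thresholds.
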